## Abstract

**Background:** Despite the rapid advance of neonatal care, bronchopulmonary dysplasia (BPD) remains a significant burden for the preterm population, and there is a lack of effective intervention. Stem cell depletion because of preterm birth is regarded as one of the underlying pathological mechanisms for the arrest of alveolar and vascular development. Preclinical and small-sample clinical studies have proven the efficacy and safety of stem cells in treating and preventing lung injury. However, there are currently no randomized clinical trials (RCTs) investigating the use of autologous cord blood mononuclear cells (ACBMNC) for the prevention of BPD in premature infants. The purpose of this study is to investigate the effects of infusion of ACBMNC for the prevention of BPD in preterm neonates <28 weeks.

**Methods:** In this prospective, randomized controlled double-blind multi-center clinical trial, 200 preterm neonates <28 weeks gestation will be randomly assigned to receive intravenous ACBMNC infusion (5 × 10^7^ cells/kg) or placebo (normal saline) within 24 h after birth in a 1:1 ratio using a central randomization system. The primary outcome will be survival without BPD at 36 weeks of postmenstrual age or at discharge, whichever comes first. The secondary outcomes will include the mortality rate, other common preterm complication rates, respiratory support duration, length, and cost of hospitalization, and long-term outcomes after a 2-year follow-up.

**Conclusion:** This will be the first randomized, controlled, blinded trial to evaluate the efficacy of ACBMNC infusion as a prevention therapy for BPD. The results of this trial will provide valuable clinical evidence for recommendations on the management of BPD in extremely preterm infants.

**Clinical Trial Registration:** ClinicalTrials.gov, NCT04440670, registered 06/18/2020, prospectively registered, https://clinicaltrials.gov/study/NCT04440670?term=NCT04440670&rank=1 (Additional File 2).

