## Methods and Analysis

### Study Design and Settings

This study protocol describes a randomized, placebo-controlled, double-blinded, multi-center trial to be conducted at 14 medical centers (Table 1) in tertiary hospitals. The participating Neonatal Intensive Care Units (NICU) were selected by the expert committee based on the distance to Guang Dong Cord Blood and Stem Cell Bank and the level of intensive care that the NICUs could provide. The Guang Dong Cord Blood and Stem Cell Bank is a public provincial blood bank affiliated with the Guangdong Women and Children Hospital and collects cord blood routinely at these hospitals. To ensure that the cord blood would be processed and infused to the infants within 24 h after birth, the distance of these centers should fulfill this criterion. Furthermore, the NICUs in the selected centers are members of Guangdong Neonate Intensive Care Network. The staff working at these centers has been trained by the NICU of the Guangdong Women and Children Hospital, which means the selected centers use similar guidelines regarding treatment of patients. All the centers will hold quality control meetings frequently to ensure research consistency. A total of 200 neonates fulfilling the eligibility criteria will be enrolled. Subsequently, the participants will be randomly divided into two groups [ACBMNC infusion group and control [placebo] group] at a 1:1 ratio. The protocol for this study has been developed based on Standard Protocol Items: Recommendations for Interventional Trials (SPIRIT) checklist (Additional File 1). We have followed the Consolidated Standards of Reporting Trials (CONSORT) guidelines and the study design is illustrated in Figure 1. Consort flow diagram.

**Table 1 T1:** Research centers.

01	Department of neonatology, Guangdong Women and Children Hospital
02	Department of neonatology, Sun Yat-sen Memorial Hospital, Sun Yat-sen University
03	Department of neonatology, The third Affiliated Hospital of Sun Yat-sen University
04	Department of neonatology, Nanfang Hospital, Southern Medical University
05	Department of neonatology, Zhongshan Boai Hospital
06	Department of neonatology, Foshan Chancheng Central Hospital
07	Department of neonatology, Foshan Women and Children Hospital
08	Department of neonatology, Guangdong Second Provincial General Hospital
09	Department of neonatology, Hexian Memorial Affiliated Hospital of Southern Medical University

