#### Sample Size

Based on our previous study and others' study (9–16, 21), we found the ACBMNC infusion was effective in reducing respiratory support duration in preterm infants. The rate of BPD among extremely preterm infants in our NICU was 60% (pA). What we expect to be an intended (or at least acceptable) effect of the ACBMNC infusion is 25% reduction in frequency of BPD (pB:35%). To detect this difference with a sensitivity of 80% (α) and an error probability of 5% (β), at least 59 patients per randomization group will be required using the following formula:

$$\begin{array}{l} \text{n}=\left(\text{pA}\left(1-\text{pA}\right)/\text{κ}+\text{pB}\left(1-\text{pB}\right)\right)\left((\text{z}1-\alpha /2+\text{z}1-\beta )/(\text{pA}-\text{pB}\right){)}^{2} \end{array}$$

To account for the possibility of as high as 20% loss to follow-up, our estimated sample size is 140 cases totally.

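### The sample-size section arrives at 140 infants while the abstract and design section plan 200, with nothing to reconcile them; 140 also falls slightly short of the section's own requirement

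*Protocol article*

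**What the plan says.** Three current statements in the protocol article give the size of the trial.

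- Abstract, Methods: "200 preterm neonates <28 weeks gestation will be randomly assigned".
- Study Design and Settings: "A total of 200 neonates fulfilling the eligibility criteria will be enrolled".
- Sample Size: "To account for the possibility of as high as 20% loss to follow-up, our estimated sample size is 140 cases totally".

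The Sample Size section takes its control rate from local experience, "The rate of BPD among extremely preterm infants in our NICU was 60% (pA"), and targets a "25% reduction in frequency of BPD (pB:35"%). It prints an unpooled two-proportion formula in z1−α/2 and z1−β, and requires no fewer than 59 per group. The error rates are introduced as "with a sensitivity of 80% (α) and an error probability of 5% (β").

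Other sections bear on how these figures can be read. Statistical Analysis plans two-tailed tests at p < 0.05, with a chi-squared test for proportions. Outcome Measures defines the primary outcome as BPD or death. Safety Assessment refers to interim analyses with sequential analysis of the primary outcome.

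**The concern.** The only total with a derivation is 140, and the total the article says it will randomise is 200. They differ by 60 infants, 43% of 140 (60/140). Screening losses do not explain the gap, because the Abstract's 200 are randomised infants and the 140 already includes the allowance for loss.

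The stakes are practical. The planned total fixes the power a reader should attach to a null result, and it is the denominator for the fraction of information at each interim look. As printed, the derived total falls below its own minimum once the stated loss occurs, and the other total has no derivation.

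**Working it through.** **Inputs.** pA = 0.60 and pB = 0.35 (Sample Size); allocation 1:1, so κ = 1 (Randomization); two-sided 5% level (Statistical Analysis); power 80% (the figure called sensitivity in Sample Size); loss 20% (Sample Size).

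**1. Reproducing the 59.** The article's formula is n = [pA(1−pA)/κ + pB(1−pB)] × [(z1−α/2 + z1−β)/(pA−pB)]².

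Variance term: 0.60×0.40 + 0.35×0.65 = 0.2400 + 0.2275 = 0.4675.

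n = 0.4675 × [(1.960 + 0.842)/0.25]² = 58.7, rounded up to 59 per group, 118 in total. This matches the article exactly, with α = 0.05 and 1−β = 0.80. The interchanged labels therefore did not enter the calculation.

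**2. Allowing for loss.**

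- To keep 118 evaluable after 20% loss: 118/(1−0.20) = 147.5, so 148 (74 per group).
- Multiplying instead: 118 × 1.20 = 141.6. The stated 140 is close to this, which suggests multiplication by 1.2 instead of division by 0.8.
- What 140 leaves: 140 × 0.80 = 112, or 56 per group, against the required 59.
- The loss that 140 can absorb: 1 − 118/140 = 15.7%.
- What 200 leaves: 200 × 0.80 = 160, or 80 per group.
- The loss at which 200 would leave 118: 1 − 118/200 = 41%. The 20% allowance therefore does not generate 200.

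**3. Power for 60% against 35%, two-sided 0.05, one fixed-sample test.**

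Unpooled (the article's formula): Φ(0.25/√(0.4675/n) − 1.960).

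Pooled (chi-squared): Φ([0.25 − 1.960·√(2·p̄(1−p̄)/n)]/√(0.4675/n)), with p̄ = 0.475.

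At n = 56, unpooled: 0.25/√(0.4675/56) = 2.736; 2.736 − 1.960 = 0.776; Φ = 0.781.

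| Evaluable per group | Unpooled | Pooled | Exact, uncorrected chi-squared |
|---|---|---|---|
| 56 (140 less 20%) | 78.1% | 76.2% | 75.5% |
| 59 (stated minimum) | 80.2% | 78.4% | 79.2% |
| 80 (200 less 20%) | 90.5% | 89.4% | 89.0% |

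A pooled calculation would ask for 62 per group before loss and 78 per group (156) after it. That choice of approximation matters less than the 140 against 200.

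**4. Endpoint.** The 60% and 35% are rates of BPD. The article gives no rate for BPD or death, so power for the primary outcome cannot be computed from it.

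**The case against.** The best defence is that both statements about what will actually be done say 200. The Sample Size section speaks of a minimum per group and an estimated total, so 140 may be a calculated floor that planned enrolment deliberately exceeds. On that reading the discrepancy errs on the safe side: 200 exceeds both 140 and 148. This reading is plausible, and it limits the consequence. A reader might infer that nobody can tell when recruitment ends, or that the trial is underpowered. Neither follows, because the enrolment statements agree with each other and 200 is ample on the article's own assumptions. But the article nowhere says that 140 is a floor or why 200 was chosen, so the contradiction stands.

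The shortfall of 140 is also fairly called small. It is 8 infants (148 − 140) and about two percentage points of power by the article's own formula, and the 20% is stated as an upper limit on loss. That stands too.

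A reader might take the interchanged α and β to mean the calculation is wrong. It is not: 59 reproduces with the conventional values, and the Statistical Analysis section confirms 5% as the significance level.

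**Conclusion.** The sample size is wrong as written and must be corrected, chiefly because two totals, 140 and 200, stand unreconciled.

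The failure of 140 to meet its own minimum is secondary. After 20% loss, power is about 78% by the article's formula and about 76% for a pooled chi-squared test, instead of 80%. It matters only if 140 is the real target. If 200 is the target, power after the same loss is about 89–90%. The α/β labels are an editorial slip.

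These powers assume BPD rates of 60% and 35%, two-sided alpha 0.05, equal groups, equal 20% loss and a single final test. A reader might carry the 89–90% over to the primary outcome. The article does not support that: its rates are for BPD alone, and the interim sequential analysis it mentions is not reflected in the calculation.

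**What to change.** State one total in the Abstract, Study Design and Settings, and Sample Size, and show how it was reached.

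- **If it is 200:** say that 59 per group is the minimum, that 148 are needed after 20% loss, and that 200 leaves 80 per group, with about 89–90% power for BPD at 60% against 35%, two-sided alpha 0.05, in a single fixed-sample test. The sponsor should give the actual reason for 200; it should not be supplied after the fact.
- **If it is 140:** correct the Abstract and Study Design and Settings, and restate power after 20% loss as about 76–78% under the same conditions.

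In either case, say that the rates are for BPD alone and not for the composite of BPD or death, and relabel the error rates as power 80% (1−β) and alpha 5%.

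The cost is a few sentences of protocol text. If 200 is the true target, no further infants are needed. If 140 is, the correction lowers the published enrolment figure and the stated power.

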#### Randomization

The randomization sequence will be generated electronically using SPSS (version 21). Following enrolment, treatment will be assigned after verification of eligibility and consent status. Computer generated randomization will be performed by the statistician in our center at a 1:1 ratio. A randomization number will be assigned by computer for each enrolled infant. Infants will be randomized to the order in which they receive ACBMNC and placebo infusions. Those enrolled in the ACBMNC group will receive an infusion of ACBMNC within 24 h after birth. Those in the placebo group will receive an infusion of a placebo solution, consisting of normal saline with the same volume. Cell dose for all patients to be targeted at 5 × 10^7^ cells per kilogram.

#### Blinding

All hospital ethics committees will review the study data during the trials. None will be involved in the study or will be aware of the treatment-group assignments for the infants. Only nurses and physicians conducting the infusions will be aware of the treatment assignment, and these individuals will have had no contact with the staff that will collect and analyze the patient data. The parents will not be aware of the treatment assignment. This study will be double-blinded.

#### Intervention

##### Cord blood processing

The Guang Dong Cord Blood and Stem Cell Bank is a public provincial blood bank accredited for stem cell manipulation by National Health Commission of the People's Republic of China and American Association of Blood Bank (AABB). Procedures for cord blood collection and processing will be performed in accordance with cord blood bank guidelines (22). The umbilical cord will be clamped for collection using a blood-collection bag (WEGO, China) containing 28 mL of citrate-phosphate-dextrose anticoagulant immediately after birth and before the placenta is delivered. The umbilical vein will be sterilized and punctured with a 17-gauge needle. UCB will be collected by trained obstetricians or cord blood bank collection staff present at the hospital during weekdays for 8–12 h per day in each center. When collection is completed, the blood bag tubing will be closed and sealed. Cord blood labeled with the full name of the donor, group type, and volume of the blood product will be stored at 4°C and sent to the Cord Blood and Stem Cell Bank for immediate processing. Before processing, 2 mL samples will be taken from all collected CB units to test for the presence of viruses (HIV, HBV, HCV, CMV) by PCR and bacterial infections via bacterial smear. A sample of peripheral blood was collected from the mother and tested for the presence of maternal transmissible diseases. The results will be obtained immediately before the start of transfusion. After a sample is taken, it will be volume- and RBC-reduced after a 30 min incubation with 6% Hespan (Bethlehem, USA) following established CBB procedures using the SEPAX S-100 automated processing system (Biosafe, Geneva, Switzerland) if the unit contained >30 mL of UCB or manually, if the unit was <30 mL. The mononuclear layer will be isolated by density gradient centrifugation (1,000 × g, 30 min, room temperature, Beckman, American), and then transferred to cryobags. Excessive nucleated cell-poor plasma will be expelled. Meanwhile, the MNC count, CD34 cell count, CFU-GM, and sterility detection (Sheldon Manufacturing Inc., Comelius, OR, USA) will be performed. Cell viability will be measured using a 7-aminoactinomycin D (7-AAD) detection kit by flow cytometry analysis (BD Bioscience, USA). After processing, the cord blood cells will be sent back to the hospitals where it was collected. All infusions will be administered at the NICU. Infusate and subject identities will be double-checked by research and clinical nursing staff. Infusions will also be monitored by research and clinical staff. Cells will be infused over 15 min, followed by a 2-mL saline flush to clear the intravascular line.

#### Trial Treatment Methods

Eligible infants will be observed at the NICU of the Guangdong Women and Children Hospital until discharge home. All patients in the study will be given intensive care therapy in accordance with departmental guidelines, which include therapies such as positive pressure mechanical ventilation, non-invasive respiratory support, oxygen therapy, and exogenous surfactant replacement (Curosurf, Chiesi, Parma, Italy). Chest radiographs will be performed at admission and 8 h after CBT on the first day of life in all surviving patients. Blood gas will be monitored every 24 h until weaning from ventilation. All clinical diagnoses will be defined according to a standard reference (16). Soon after the preterm infant is delivered, written consent will be obtained from the parents, and ACBMNC infusion was applied to the baby in addition to routine pulmonary surfactant replacement, and mechanical ventilation support as indicated. Those assigned to the ACBMNC group will receive an infusion of ACBMNC with 24 h after birth. Infants in the control group will receive an infusion of a placebo solution consisting of normal saline with the same volume. Cell dose for all patients will be targeted at 5 × 10^7^ cells per kilogram.

#### Safety Assessment

The trial will be strictly monitored by a safety monitoring board, which will be notified of specific severe adverse events (including death, LOS, NEC, severe IVH, cystic periventricular leukomalacia, and fever) within 48 h. Other adverse or unexpected events will be reviewed monthly. After each interim analysis, the data safety monitoring board will make a decision on whether to stop or continue the trial based on safety monitoring and sequential analysis of the primary outcome. Assessment of safety will be conducted at 12 and 24 h after infusion, as well as during hospitalization and return visits. Heart rate, systolic, diastolic, and mean arterial blood pressure, and arterial blood oxygen saturation levels will be monitored in the peripheral blood continually and will be documented. Moreover, laboratory investigations in the peripheral blood including blood routine tests and blood gas analysis will be monitored and kept stable during the whole treatment period. Infusion reactions and signs of circulatory overload will be checked.

#### Basic Clinical Data Collection

The following data will be collected: (1) clinical basic characteristics including sex, gestational age, birth weight, delivery mode, Apgar score at 1, 5, 10 min; (2) characteristics of cord blood processing including cord blood volume, cell number, cell concentration before and after processing, CFU-GM, CD34+ cell count, cell viability post processing; (3) characteristics of infusion cells including total cell number, time between collection (birth) and initiation of infusion, infused volume, and pathogen detection (including bacteria culture, fungus culture, HIV, HBV, HCV, CMW, and *Treponema pallidum*) results; and (4) other routine clinical interventions including dose and times of pulmonary surfactant (PS) replacement, postnatal steroid use, surgical closure of patent ductus arteriosus, and use of blood products.

We will use the following clinical definitions in this study:

Gestational age will be determined on the basis of a combination of the last menstrual period and early ultrasound findingsThe diagnosis of common preterm complications will include the following (23):

BPD, defined as treatment with oxygen >21% for at least 28 days, and its severity will be assessed at 36 weeks of postmenstrual age or discharge home whichever comes first. Mild BPD, defined as breathing room air at assessment. Moderate BPD, defined as the need for <30% supplemental oxygen, and severe BPD defined as needing ≥30% supplemental oxygen or positive airway pressure. For these patients, BPD status will be analyzed by a committee of three independent experts blinded to the study group.

RDS will be defined if the infants show evidence of respiratory symptoms such as grunting and chest retraction, typical chest radiograph findings, and/or treatment with surfactant, and the need for assisted ventilation.

NEC will be defined using Bell's classification. Infants with stage II or above will be diagnosed with NEC.

LOS will be defined if the infants had a positive bacterial culture results after the first 72 h after birth.

ROP will be defined according to the International Classification for Retinopathy of Prematurity.

Anemia will be defined as hemoglobin no more than 140 g/L.

IVH and periventricular leukomalacia (PVL) will be defined by serial head ultrasound, performed according to the description by Volpe. The first head ultrasound will be performed within 3 days after birth and follow-up head ultrasound examinations will be performed every week until the day of discharge.

VAP will be defined as a pneumonia occurring after the patient has been intubated and has received mechanical ventilation for more than 48 h.

### Outcome Measures

*Primary outcome measure:*

- The frequency of BPD or death in at 36 weeks of postmenstrual age or discharge home whichever comes first.

*Secondary outcome measures:*

- Mortality rate- Incidence of BPD- Incidence of other preterm complications including IVH, PVL, NEC, ROP, RDS, VAP, LOS, and anemia [all clinical diagnoses will be defined according to a standard references (16)].- Duration of hospitalization.- Duration of mechanical ventilation and oxygen therapy- Frequency of re-intubation.- The time (days) return to BW.

#### Follow Up

All the infants will be followed until the corrected age of 2 years old, the following parameters will be recorded.

- Anthropometric characteristics: weight, length, and head circumference.- Respiratory outcomes including the occurrence of wheezing, asthma, nocturnal cough, supplemental oxygen requirement, and rehospitalization because of pneumonia.- Degree of neurodevelopmental impairment via standardized neurological examination [using the revised Brunet-Lézine [RBL] global developmental quotient score (16)], and other major neurodevelopmental outcomes including cerebral palsy, seizures, auditory impairment, and visual impairment (Table 2).

**Table 2 T2:** Contents and points of data capture: Standard Protocol Items: Recommendations for Interventional Trials (SPIRIT) schedule of enrolment, interventions, and assessments.

**Visit**	**Screening**	**Intervention**	**Follow up**	
	**V1**	**V2**	**V3**	**V4**
Time point	born	Within 24 h after birth	36 weeks of postmenstrual age	Corrected age of 2 years old
Informed consent form	√			
Screening the subject	√			
Demographic information	√			
Inclusion/exclusion criteria	√			
Get random number	√			
Cord blood process		√		
Vital signs	√	√	√	
Chest radiographs		√		
Pulmonary surfactant replacement		√		
Mechanical ventilation	√	√		
Arterial blood oxygen saturation	√	√		
Laboratory tests	√	√	√	
Blood routine test	√	√		
Blood gas	√	√		
Safety outcomes		√	√	√
Record adverse events		√	√	√
Postnatal steroid use		√	√	√
Surgical closure of patent ductus arteriosus		√	√	
Blood products use		√	√	
Bronchopulmonary dysplasia			√	
Other preterm complications			√	
Duration of hospitalization			√	√
Anthropometric Characteristics			√	√
Respiratory Outcomes				√
Neurodevelopmental outcomes				√

### Statistical Analysis

Statistical analyses between the two groups will be performed using an unpaired two-tailed Student's *t*-test or Chi-squared Test as appropriate. A logistic regression model will be used for the entire study population (i.e., without removing deaths) to adjust for the effect of treatment on primary outcome according to baseline characteristics and events known to affect the occurrence of BPD (i.e., gestational age, birth weight and other characters that are different in two groups after initial analysis), and to investigate the effect of treatment on the following outcomes: extubation rates, severe adverse events, and death before discharge. The Breslow-Day test and Corchran-Mental-Haenszel (CMH) test will be used to adjust the data derived from different participating centers. The results will be reported as odds ratio (OR) with 95% confidence intervals (CI). All statistical tests will be two-tailed and a *p* < 0.05 will be considered statistically significant. All statistical analysis will be performed using SPSS 21.0 (IBM).

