#### Secondary Objectives

The secondary objectives of this trial are (1) to compare the infant mortality rate at 36 weeks of postmenstrual age; (2) to compare the rate of other common preterm complications included intraventricular hemorrhage (IVH), necrotizing enterocolitis (NEC), retinopathy of prematurity (ROP), respiratory distress syndrome (RDS), ventilation-associated pneumonia (VAP), hypoxic ischemic encephalopathy (HIE), late-onset sepsis (LOS), and anemia; (3) to compare the duration of mechanical ventilation and oxygen therapy in the two groups; (4) to determine re-intubation rate and time return to birth weight (BW); (5) to compare the duration of antibiotic usage; and (6) to determine the long-term outcomes after a 2-year follow up, including anthropometric characteristics, respiratory outcomes, and neurodevelopmental outcomes via standardized neurological examination.

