### Participants

#### Inclusion Criteria

Infants fulfilling all the following inclusion criteria will be enrolled in this trial: (1) birth at a study hospital; (2) a singleton birth; (3) <28 weeks gestational age, (4) signed informed consent from parents before labor; and (5) available umbilical cord blood (UCB).

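### The t-test, the only method named for duration outcomes, says nothing of deaths; if mortality differs between arms, the arm with more early deaths can appear to need shorter support

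*Protocol article*

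**What the plan says.** In the protocol article, Outcome Measures lists among the secondary outcomes "Duration of mechanical ventilation and oxygen therapy", "Duration of hospitalization" and the number of days to regain birth weight. Secondary Objectives commits to a between-arm comparison: "to compare the duration of mechanical ventilation and oxygen therapy in the two groups".

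Statistical Analysis opens with "Statistical analyses between the two groups will be performed using an unpaired two-tailed Student's" t-test, or a chi-squared test, as appropriate. It ties neither test to a named outcome, but the t-test is the only method given that can apply to a number of days.

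Deaths are mentioned once: "A logistic regression model will be used for the entire study population (i.e., without removing deaths". That sentence covers the primary outcome, extubation rates, severe adverse events and death before discharge. It does not cover the durations.

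The protocol expects deaths. Infants are "<28 weeks gestational age", mortality is a secondary outcome, and the primary outcome is "The frequency of BPD or death in at 36 weeks of postmenstrual age or discharge home whichever comes first".

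**The concern.** A duration of support or stay cannot run past death. An infant who dies on day 3 while ventilated has 3 ventilator days, numerically one of the most favourable values in the trial. A t-test on durations can treat such infants in two ways, and the text does not choose between them.

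- **Deaths included.** Early deaths enter as short durations, so the arm with more of them has a lower mean.
- **Survivors only.** The groups compared are defined by an event after randomisation that treatment may affect. If the sicker infants die, the arm that loses more of them keeps a healthier remainder.

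Neither is a sound randomised comparison when mortality differs, and mortality is itself an outcome the trial compares. The Background reports the group's earlier study as showing benefit on ventilation and oxygen days, and Sample Size cites shorter respiratory support as part of the rationale. A misleading result on these outcomes could therefore be read as support for the treatment, or against it.

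**Working it through.** **The plan's own figure.** No figure is given for the durations. The only sample-size figure, 59 per group, concerns BPD frequency. It reproduces: (0.60×0.40 + 0.35×0.65) × ((1.960 + 0.842)/0.25)² = 0.4675 × 125.6 = 58.7, rounded up to 59. It does not bear on this point.

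**Inputs from the document.** Two-sided 5% test and 1:1 allocation. "A total of 200 neonates fulfilling the eligibility criteria will be enrolled" gives 100 per arm; the 140 in Sample Size gives 70 per arm. Both sizes were run.

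**Assumed inputs, because the document gives none.** Underlying ventilator days T are lognormal with median 20 and log-SD 0.8, the same in both arms. Infants who die do so at an exponential time D with mean 7 days, independent of T. Mortality is 15% to 30%.

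**Deaths included: shift in the mean.**
- Mean of T: 20 × exp(0.8²/2) = 27.5 days.
- Mean recorded value in an infant who dies, E[min(T, D)]: 6.1 days (by simulation).
- Mean recorded value in an arm with mortality m: (1 − m) × 27.5 + m × 6.1.
- Difference between arms: mortality gap × (27.5 − 6.1) = mortality gap × 21.4 days.

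This gives 0.05 × 21.4 = 1.1 days, 0.10 × 21.4 = 2.1 days and 0.15 × 21.4 = 3.2 days.

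**Deaths included: rejection by the t-test** (20,000 simulated trials per setting).

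| Mortality, control vs treated | Mean days | Rejection, 70 per arm | Rejection, 100 per arm |
|---|---|---|---|
| 15% vs 15% | 24.3 vs 24.3 | 5% | 5% |
| 15% vs 20% | 24.3 vs 23.3 | 6% | 6% |
| 15% vs 25% | 24.3 vs 22.2 | 8% | 9% |
| 30% vs 15% | 21.1 vs 24.3 | 13% | 16% |

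Small changes in how a death is recorded, and repeated runs, give 5 to 6%, 8 to 9% and 12 to 17% for the last three rows. In the last two rows nearly all significant results favour the arm with more deaths.

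**Sensitivity to the assumed distribution.** With gamma durations (mean 30 or 80 days, shape 1 or 4) at 100 per arm, 15% vs 20% mortality gives 6 to 8% rejection, 15% vs 25% gives 9 to 21%, and 15% vs 30% gives 14 to 39%. The larger values come from the less variable durations (shape 4).

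**Survivors only.** If death is unrelated to T, the survivors-only t-test keeps about 5% in every setting. If sicker infants die, it does not. With the log-odds of death rising by 0.5, 1.0 or 1.5 per SD of log T (5,000 trials), 30% vs 15% mortality and 100 per arm, rejection is 6%, 12% and 19%, again mostly favouring the higher-mortality arm. With equal mortality it stays at about 5%.

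**The case against.** The strongest objection is that this is a condensed article and that handling of death in secondary outcomes belongs in an analysis plan that is not shown. The article nowhere says that an early death counts as a short duration, nor that survivors alone are analysed. A reader might infer that the plan scores deaths as favourable values; the text does not support that. What remains is narrower: the article does name a test, it is the only one that fits these outcomes, and neither way of applying it is sound when mortality differs. The link between t-test and durations is an inference, though a close one.

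Three further objections stand in part.

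- **The effect is conditional and often small.** At equal mortality there is none, and at a 5-point gap the rejection rate barely moves. Every mortality and duration input is assumed.
- **No duration effect is reversed.** A reader might infer that the test turns a true effect around. The simulations assume no effect on underlying duration, so they show a spurious difference, not a reversal. Likewise, a rank test on ventilator-free days that detects the lower-mortality arm is detecting the mortality difference scored into the measure.
- **Skewness is a weak ground.** The t-test held its level at 70 and 100 per arm, so right skew alone is not a reason to drop it.

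It is also fair that mortality is reported separately, so an attentive reader could see the imbalance behind such a difference. That limits the harm but does not make the comparison itself interpretable.

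**Conclusion.** The concern holds in a conditional form. As written, the plan compares durations by t-test without a rule for infants who die, and the result can mislead if mortality differs and deaths come before weaning or discharge. Under the main assumptions the spurious difference is about 1, 2 or 3 days for mortality gaps of 5, 10 or 15 points, with about 5 to 6%, 8 to 9% and 12 to 17% rejection. Other plausible distributions give more. A survivors-only analysis is safe only if death is unrelated to underlying duration, which cannot be presumed in infants under 28 weeks.

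A reader might infer that the trial's main conclusion is at risk. It is not: the primary composite already counts death, and only secondary outcomes are affected. The change should be made, but the trial does not stand or fall on it.

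**What to change.** - **Ventilation and oxygen.** Make the between-arm comparison days alive and free of support from birth to 36 weeks postmenstrual age, with death before 36 weeks scored 0 (worst), by a rank-based test. State how infants discharged before 36 weeks are counted. The choice among rank-based tests and effect estimates is a matter of preference.
- **Hospital stay and return to birth weight.** Analyse time to discharge alive and time to regained birth weight, with death as a competing event.
- **Durations in survivors.** Report descriptively, beside mortality in each arm.

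The cost is analysis wording. Durations and mortality are already outcomes; dates of death, weaning and discharge need to be on file, and no new visit or procedure is required. The downside is that days alive and free of support mixes mortality with duration and so answers a different question from duration alone. Both components must be shown next to it, so that a difference driven by deaths is not read as faster weaning.
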